### Allocation concealment, assignment of interventions and blinding

After baseline assessment, participants will be randomly assigned into one of the three groups on a 1:1:1 basis using the method of permuted block, with random block sizes between 3, 6, and 9, and will be informed of their assigned group by an independent person not involved in the assessment. The allocation list will be computer-generated by an independent researcher and concealed from other researchers and participants until the time of assignment.

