#### Primary outcomes

*Hospital Anxiety and Depression Scale (HADS)* (Chinese-Cantonese) will be used to measure anxiety and depression as primary outcomes [40]. HADS is a self-report questionnaire consisting of anxiety and depression subscales. Each subscale consists of seven items and each item is rated on a four-point scale. A high score represents a high level of psychological distress. The Cronbach alphas for the HADS-anxiety and HADS-depression subscales were 0.86 and 0.78 and construct validity is evident especially when no somatic symptom assessment is included, as such symptoms may be confused with Parkinsonian manifestations [41]. The test-retest reliability for subscales, as assessed by intraclass correlation coefficient (ICC), were 0.86 and 0.84 for the HADS-anxiety and HADS-depression [42].

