### Sample size estimation

To account for multiplicity, we consider 2.5% as the nominal level of significance by Bonferroni adjustment. Taking psychological distress as the primary outcome, a previous systematic review reported an effect size of 0.4 for meditation compared to cognitive behavioral therapy control [53], while our previous clinical trial reported an effect size of 0.6 for yoga compared to exercise control [39]. Taking a conservative approach, although the comparison is made to usual care, we anticipate a moderate effect size of 0.6 for the primary outcome. Using power analysis software Gpower 3.1, assuming an attrition rate of 20%, 168 participants will give a three-arm (56 each arm) RCT 80% power to detect an effect size of 0.6 at 2.5% level of significance.

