### Data analysis

Descriptive statistics will be used to summarize the socio-demographic characteristics and clinical data (as listed above) of all subjects at all time points. Generalized estimating equations (GEE) with unstructured working covariance matrix at the individual level with repeated measurements will be performed to compare all outcomes [1–5] between groups (i.e., time effect, group effect, group*time effect). An intention-to-treat principle will be adopted. Multiple imputations will be used to account for missing data, and reporting will follow the guideline published in *BMJ* [54]. Sensitivity analysis will be performed to compare the results between complete and non-complete cases. All demographic and clinical variables (e.g. age, gender, religiosity, expectation on treatment credibility, etc.) will be accounted for in the analysis. Both crude and adjusted GEE model analyses will be performed. All statistical tests will be two-tailed and statistical significance will be set at 0.025. IBM SPSS 25.0 will be used.

Path analysis will be used to examine the mediating role of biomarkers and level of mindfulness on the effect of mindfulness training on psychological distress. Based on the hypothesized mediation model (Fig. 2), a baseline path model will be first built, then a path model with the same structure for T1 will be added and linked by intra-correlations among the same variables. The mediation effects of biomarkers and level of mindfulness on the effect of mindfulness training on psychological distress will be assessed through the significance of the corresponding products of indirect path coefficients from mindfulness training to psychological distress, respectively [55]. In view of the possibility of violation of normality assumption, a bootstrapping approach, instead of the conventional multivariate delta method, will be used to estimate the standard errors and the confidence intervals of the product terms (mediation effects) [56]. The path analyses and the bootstrapping will be performed using IBM SPSS 25.0.

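### For the two-test family implied by the 0.025 level, Holm's procedure gives the same 5% family-wise guarantee as fixed Bonferroni and never rejects less: a cheap improvement, not an error

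*Protocol article*

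**What the plan says.** The Sample size estimation section of the protocol article states the multiplicity rule: "To account for multiplicity, we consider 2.5% as the nominal level of significance by Bonferroni adjustment". The Data analysis section carries it into the tests: "All statistical tests will be two-tailed and statistical significance will be set at 0.025". Neither section names a step-down rule, and neither says which two tests share the 5%.

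The same sample size section gives the planning figures: "we anticipate a moderate effect size of 0.6 for the primary outcome", "assuming an attrition rate of 20"%, and "168 participants will give a three-arm (56 each arm) RCT 80% power to detect an effect size of 0.6 at 2.5% level of significance". For meditation it cites a review that "reported an effect size of 0.4 for meditation compared to cognitive behavioral therapy control". For yoga it cites the team's own earlier trial, with 0.6. Patients are "randomly assigned into one of the three groups on a 1:1:1 basis". Under Primary outcomes, HADS "will be used to measure anxiety and depression as primary outcomes", so there are two primary subscales. Aims and hypothesis compares each technique with usual care, at the end of the intervention and at the 4-month follow-up.

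**The concern.** Under single-step Bonferroni each comparison must reach 0.025 whatever the other one shows. Holm's procedure tests the smaller p-value at 0.025 and, only if that is significant, the other at 0.05. For two tests it controls family-wise error at 5% under any dependence, and it can never reject less than Bonferroni.

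The trial asks about each technique separately, so the second comparison matters. Suppose yoga gives p = 0.010 and meditation p = 0.035. The plan must call meditation non-significant, because 0.035 > 0.025. Holm calls both significant, because 0.010 ≤ 0.025 and then 0.035 ≤ 0.05. The loss under the plan falls mostly on the arm with the smaller effect, and the protocol's own cited figures make meditation the likelier one.

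**Working it through.** **Inputs from the protocol article.** Two-sided level 0.025; standardised effect 0.6, with 0.4 for meditation as the alternative; 56 per arm; 20% attrition; equal allocation. Evaluable per arm: 56 × 0.8 = 44.8, taken as 45.

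**Assumptions not in the documents.** A comparison of means at one time point stands in for the GEE. There is no gain from baseline adjustment. The pooled variance has 3 × 45 − 3 = 132 degrees of freedom.

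**The plan's own figure.** The mean of the test statistic is d × √(n/2) = 0.6 × √22.5 = 2.846. The two-sided 0.025 critical value with 132 df is 2.267, which gives power of about 0.72 (0.71 from a two-group t test, 0.73 from the normal approximation). The stated 80% is therefore not reproduced at two-sided 0.025. One-sided 0.025, which is two-sided 0.05, gives 0.80. That is a separate matter; here it only sets the starting value at 0.72.

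**Correlation of the two tests.** They share the control arm, so the correlation is (1/n) / (2/n) = 0.5.

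**Decision rules.**
- Bonferroni rejects A if p_A ≤ 0.025.
- Holm rejects A if p_A ≤ 0.025, or if p_A ≤ 0.05 and p_B ≤ 0.025.
- So Holm's power for A is Bonferroni's power plus P(0.025 < p_A ≤ 0.05 and p_B ≤ 0.025).

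**Results** (simulation, 1,000,000 draws per row, Bonferroni → Holm):

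| Effects (yoga, meditation) | Yoga | Meditation | Both | At least one |
|---|---|---|---|---|
| 0.6, 0.6 | 0.718 → 0.770 | 0.718 → 0.770 | 0.581 → 0.686 | 0.855, unchanged |
| 0.6, 0.4 | 0.718 → 0.736 | 0.359 → 0.446 | 0.319 → 0.424 | 0.758, unchanged |
| 0.6, 0 | 0.718 → 0.719 | 0.025 → 0.041 (error) | – | 0.728, unchanged |
| 0, 0 | – | – | – | 0.046, unchanged (family-wise error) |

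**Consistency check.** Each extra Holm rejection turns one success into two, so the gain for both arms equals the sum of the per-arm gains. For 0.6 and 0.4: (0.736 − 0.718) + (0.446 − 0.359) = 0.018 + 0.087 = 0.105, and 0.319 + 0.105 = 0.424, as tabulated.

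When only yoga works, Holm uses more of the allowance on meditation (0.041 against 0.025) but stays within 5%. A normal-theory calculation gives nearly the same gains: 72.8% to 78.0% per arm, 59.2% to 69.5% for both arms, and 36.5% to 45.3% for meditation at 0.4.

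**The case against.** **Bonferroni is valid and prespecified.** The two sections agree with each other, and no wrong conclusion follows from the rule. It also gives simple simultaneous intervals that always match the decision, which Holm does not. All of this stands. A reader might infer that the plan gives power away for nothing; the matching intervals are a real return, so the documents do not support that. What remains is a choice that can be bettered cheaply.

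**The gain is conditional.** The probability of at least one significant result is identical under both rules, and yoga gains almost nothing if meditation has no effect. This also stands. The gain matters here because the aims ask about each technique.

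**The family is not defined.** This is the strongest objection. A reader might infer that Holm beats the plan's rule whatever family is adopted, or for every test in the trial. The documents do not support that. Two arms and two HADS subscales make four contrasts, and two follow-up times make eight. Fixed 0.025 then bounds family-wise error at 4 × 0.025 = 10% or 8 × 0.025 = 20%. For four contrasts under the global null it is about 8%, taking an assumed subscale correlation of 0.6 (7.9% to 8.9% for correlations of 0.7 down to 0.3). Four-test Holm would start at 0.05/4 = 0.0125, stricter than the plan. Against the plan's 0.025, with effects of 0.6 and 0.4 and correlation 0.6, yoga's power would fall from 0.72 to 0.67 and meditation's would barely move (0.36 to 0.37). Holm would then be a correction of error control, not a uniform gain in power. The point therefore holds only for a two-test family.

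**Conclusion.** The concern holds as a cheap improvement, not as an error. The stated level is 0.05/2. For the pair that this implies, Holm keeps the 5% family-wise guarantee and never rejects less.

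At 45 evaluable per arm the gain is about 5 points per arm and 10 points for both arms if both effects are 0.6, and about 9 points for meditation if its effect is 0.4. The chance of at least one success gains nothing. Even with Holm, per-arm power of about 0.77 stays below the stated 80%.

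That Holm never rejects less in a two-test family needs no distributional assumption. The sizes rest on the simplified comparison of means and on the protocol's effect and attrition figures. Reading the pair as the two arm-versus-usual-care comparisons is an inference from 0.05/2 and the aims, because the protocol does not say so.

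**What to change.** In the Data analysis section, exempt the primary comparisons from the blanket 0.025 level and add wording such as: *For a given primary outcome and time point, the comparisons of yoga and of meditation with usual care form the family. They will be tested with Holm's procedure at a two-sided family-wise level of 5%: the smaller p-value at 0.025 and, if that is significant, the other at 0.05.*

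Keep 97.5% confidence intervals for reporting, and keep 0.025 in the sample size section as the first-step level.

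**Cost.** The change is a short text edit with no extra patients, to be made before unblinded data are seen. An interval can include zero when Holm declares significance, so the report should say that the decision follows Holm. The wording protects 5% within each pair only. If the sponsor wants 5% across both subscales or both time points, that larger family must be declared, and its first Holm step would be below 0.025.

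### The planning effect of 0.6 is called conservative for both arms but is unsupported for meditation, and at 0.6 the stated two-tailed 0.025 and 20% attrition give about 71% power, not 80%

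*Protocol article*

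**What the plan says.** All planning figures stand in the protocol article under Sample size estimation. For meditation, "a previous systematic review reported an effect size of 0.4 for meditation compared to cognitive behavioral therapy control". For yoga, "our previous clinical trial reported an effect size of 0.6 for yoga compared to exercise control". One value then serves both comparisons: "Taking a conservative approach, although the comparison is made to usual care, we anticipate a moderate effect size of 0.6 for the primary outcome". On error rate, "we consider 2.5% as the nominal level of significance by Bonferroni adjustment". The conclusion is that "168 participants will give a three-arm (56 each arm) RCT 80% power to detect an effect size of 0.6 at 2.5% level of significance", and this is reached "assuming an attrition rate of 20" per cent. That section does not say whether the 2.5% is one- or two-sided. Data analysis does: "All statistical tests will be two-tailed and statistical significance will be set at 0.025". Study design and setting says that each technique is evaluated separately against usual care, so the power statement has to hold for two pairwise comparisons.

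**The concern.** Two separate things look wrong in one short paragraph.

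First, the larger of the two cited effects is used for both arms under the label conservative. The only reason visible in the text is that an active-control effect is carried over to a usual-care comparison without claiming the extra benefit expected against a weaker comparator. That reasoning yields 0.6 for yoga. Applied to meditation, it yields 0.4. To reach 0.6 for meditation one must count on a larger effect against usual care, which is the opposite of a conservative step, and the article does not say by how much.

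Second, the 80% does not follow from the level, sidedness and attrition that the article states, even if 0.6 is accepted.

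At stake is how a non-significant result is read, above all for meditation. A reader told that each comparison had 80% power at a conservative effect would give such a result more weight than the design supports.

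**Working it through.** **Inputs.** 56 randomised per arm, 20% attrition, d = 0.6, level 2.5% (Sample size estimation); two-tailed (Data analysis); 1:1:1 allocation (Allocation concealment section). Evaluable per arm: 56 × 0.8 = 44.8.

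**Method.** Two-sample t-test, SD = 1, unadjusted. Degrees of freedom are 2n − 2, the noncentrality is d × √(n/2), and power is the probability that the noncentral t exceeds the critical value.

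**Reproducing the plan's figure.**
- Required n for 80% at d = 0.6, two-sided 0.025. Normal approximation: 2 × (2.2414 + 0.8416)² / 0.36 = 52.8, so 53 per arm. By the t-test: 55 per arm. After division by 0.8: 67 or 69 per arm, 201 or 207 in total. The article has 168.
- Power with n = 44.8: noncentrality 0.6 × √22.4 = 2.840, critical value 2.281, power 71.1% (72.5% by the normal approximation). The stated 80% does not reproduce.
- Two other readings come close to 168:
  - (a) One-sided 0.025 with 20% attrition needs 45 per arm; 45 / 0.8 = 56.25, and power at 44.8 is 80.2%.
  - (b) Two-sided 0.025 with no allowance for attrition needs 55 per arm, and power at 56 is 81.5%.

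  Reading (a) departs from the stated two-tailed tests, and reading (b) from the stated attrition.

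**Power by assumed effect (t-test).**

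| Effect | Two-sided 0.025, 44.8 per arm (as stated) | Reading (a): one-sided 0.025, 44.8 per arm | Reading (b): two-sided 0.025, 56 per arm |
|---|---|---|---|
| 0.6 | 71% | 80% | 82% |
| 0.5 | 54% | 65% | 65% |
| 0.4 | 35% | 47% | 44% |

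The first row isolates the sidedness and attrition problem. Reading down a column isolates the choice of effect.

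**Baseline adjustment (assumption).** If adjustment for baseline with correlation r reduces the residual SD by √(1 − r²), the effect to enter is d / √(1 − r²). The article gives no such correlation, so a range of r is assumed. At d = 0.4 with 44.8 per arm, two-sided 0.025:
- r = 0.3: effect 0.419, power 39%
- r = 0.5: effect 0.462, power 47%
- r = 0.7: effect 0.560, power 64%
- r = 0.8: effect 0.667, power 81%

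At d = 0.6 the same adjustment gives about 76% at r = 0.3 and 84% at r = 0.5.

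**The case against.** The strongest reply concerns the comparator. The 0.4 is meditation against cognitive behavioral therapy, whereas this trial compares meditation with routine outpatient care. If meditation truly exceeds cognitive behavioral therapy by 0.4, its effect against usual care is 0.4 plus whatever that therapy adds over usual care. An addition of 0.1 would give 54% power, and an addition of 0.2 would meet the planning value (illustrative amounts; the article gives none). This stands. A reader might infer that meditation has only 35% power on the plan's own evidence, or that the plan contradicts itself by using 0.6. The article supports neither: it never states an effect for meditation against usual care, and it acknowledges the change of comparator.

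A reader might also put the whole fall from 80% to 35% down to the effect size. That is not right either. Part of it, 80% to 71%, arises at 0.6 from sidedness and attrition. Like for like, on the readings that roughly reproduce 168, the fall is from 80–82% to 44–47%.

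Nor should one infer that a finding of yoga effective and meditation not is to be expected. Simulation with a shared control and assumed true effects of 0.6 and 0.4 gives that pattern in about 40% of trials, which is below even odds. No test of yoga against meditation is described.

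Finally, the planned analysis is a repeated-measures GEE, crude and adjusted, and not a t-test, so actual power may be higher. This stands as a limit on the figures. But the article gives no correlation from which to claim the gain, and it does not say that its 80% rests on one. Powering two arms on a common target effect is an ordinary choice. The fault is the label and the stated power.

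**Conclusion.** The point holds in two parts.

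The label conservative is supported for yoga only. For meditation, 0.6 is unsupported by any figure in the article, though not shown to be wrong.

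The stated 80% at 0.6 is about 71% for each comparison under the article's own two-tailed 0.025 and 20% attrition. This assumes an unadjusted comparison of two means and that participants lost to attrition contribute no information.

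The 35% at 0.4 and 54% at 0.5 are sensitivity figures for meditation, not predictions. They are conditional on the effect against usual care being that size and on no gain from baseline adjustment.

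**What to change.** Revise the wording of Sample size estimation:

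1. Remove the word conservative for meditation, or justify 0.6 for meditation against usual care with a figure.
2. Restate power as about 71% at 0.6 for each comparison with usual care (two-sided 0.025, 20% attrition, unadjusted).
3. Add a sensitivity range for meditation: about 35% at 0.4 and 54% at 0.5. Note that 0.4 comes from an active-control comparison, so the effect against usual care may be larger, and that on the readings that roughly reproduce 168, power at 0.4 is 44% to 47%.
4. If a gain from baseline adjustment is claimed, state the assumed correlation. At 0.4, power runs from about 39% at r = 0.3 to 81% at r = 0.8.

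The cost is a rewritten paragraph and a less favourable stated power. No additional patients and no change to the analysis are proposed.

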**Methods:**

We will conduct an assessor-blind three-arm randomized waitlist-controlled trial with a descriptive qualitative evaluation. Up to 168 PD patients will be recruited from community settings and out-patient clinics, and randomized to meditation, yoga, or usual care group. Meditation and yoga sessions of 90-minute are held weekly for 8 weeks. Primary outcomes include anxiety and depression. Secondary outcomes include PD-related motor and non-motor symptoms and quality-of-life; and level of mindfulness and biomarkers of stress and inflammatory responses will be measured as mediating variables. All outcome evaluations will be assessed at baseline, 8 weeks, and 24 weeks. Following the intention-to-treat principle, generalized estimating equation models and path analysis will be used to identify the treatment effects and the mediating mechanisms. A subsample of 30 participants from each intervention group will be invited for qualitative interviews.

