## Methods

### Study design and setting

This is a multi-centre, assessor-blinded, 3-arm randomised waitlist-controlled trial with sequential mixed-method design to evaluate the effect and acceptability of 8-week programs using individual mindfulness techniques (yoga alone and meditation alone), compared to wait-list usual care control. Figure 1 shows the CONSORT flow diagram. Repeated outcome measures will be assessed at three time points across the 6-month study period to quantitatively evaluate the immediate and sustained effects of each mindfulness technique on anxiety and depression and other physio-psycho-spiritual outcomes in PD patients, compared with the usual care control group. Assessment time points are: baseline (Prior to randomization, T_0_), 8 weeks (T_1_: 1-week post-intervention), and 24 weeks (T_2_: 4-month post-intervention).

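### The stated 80% power does not follow from the plan's own inputs: at two-tailed 0.025 with 20% attrition, 168 patients give about 71%

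*Protocol article*

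**What the plan says.** The Sample size estimation section of the protocol article opens with the significance level: "To account for multiplicity, we consider 2.5% as the nominal level of significance by Bonferroni adjustment". It then sets the effect, "we anticipate a moderate effect size of 0.6 for the primary outcome", names Gpower 3.1 as the software, assumes 20% attrition, and concludes that "168 participants will give a three-arm (56 each arm) RCT 80% power to detect an effect size of 0.6 at 2.5% level of significance". It does not say whether the 2.5% is one-sided or two-sided.

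The Data analysis section settles that for the trial's tests: "All statistical tests will be two-tailed and statistical significance will be set at 0.025".

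Three further statements fix how the numbers must be read:

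- The abstract's Methods paragraph makes 168 the number entering the trial, not the number completing it: "Up to 168 PD patients will be recruited from community settings and out-patient clinics".
- Patients are "randomly assigned into one of the three groups on a 1:1:1 basis", so there are 56 per arm at randomisation.
- The design section says that the trial is to "evaluate the immediate and sustained effects of each mindfulness technique on anxiety and depression", in comparison with usual care. The comparisons of interest are therefore pairwise, each active arm against control.

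**The concern.** The sample size paragraph announces a multiplicity adjustment and an attrition allowance, but the final number looks too small to contain both. If 56 per arm is the figure before attrition, about 45 per arm remain. For an effect of 0.6, 45 per arm is a familiar requirement at two-sided 0.05, not at two-sided 0.025.

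At stake is the trial's main design claim. Readers use the stated power to judge how much a non-significant arm tells them. If the chance of missing a true effect of 0.6 is nearer 29% than 20%, a null result for yoga or meditation is weaker evidence than the protocol implies. The protocol's own Limitations section warns of high attrition, and losses beyond 20% would lower the power further. Type I error and the validity of the estimates are not affected.

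**Working it through.** **Inputs.** From Sample size estimation: standardised difference d = 0.6, level 2.5%, attrition 20%, 56 per arm, stated power 80%. From Data analysis: two-tailed testing at 0.025. One assumption is added: 0.6 is a standardised mean difference in a two-group comparison. This fits the between-group effect sizes of 0.4 and 0.6 that the protocol cites.

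**Evaluable patients per arm.** 56 × (1 − 0.20) = 44.8, about 45.

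**Formulae (normal approximation, equal arms).**

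- Power ≈ Φ(d√(n/2) − z), where z is the critical value.
- n per arm = 2(z + z₀.₈)² / d², with z₀.₈ = 0.842.

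The t-test figures below use the noncentral t distribution in place of the normal.

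**Step 1: find what reproduces the stated figure.** At two-sided 0.05, which has the same critical value as one-sided 0.025, z = 1.960.

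- n = 2(1.960 + 0.842)² / 0.36 = 43.6, so 44. The t-test needs 44.6, so 45.
- Inflating for attrition, 44.6/0.8 = 55.75 and 45/0.8 = 56.25, either side of the protocol's 56. (Strict rounding up from 45 would give 57.)
- With 44.8 per arm: 0.6 × √22.4 = 2.840, and Φ(2.840 − 1.960) = 81.0%. The t-test gives 80.2%.

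This reproduces 80% at 56 per arm.

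**Step 2: use the level the plan specifies.** At two-sided 0.025, z = 2.241.

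- With 44.8 per arm: Φ(2.840 − 2.241) = 72.5%. The t-test gives 71.1%.
- n for 80% power = 2(2.241 + 0.842)² / 0.36 = 52.8, so 53. The t-test needs 54.1, so 55.
- After attrition: 55/0.8 = 68.75, so 69 per arm and 3 × 69 = 207 in total. By the normal approximation, 53/0.8 = 66.25, so 67 per arm and 201 in total.

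**Step 3: test whether omitting attrition explains it.** With all 56 per arm analysed at two-sided 0.025: 0.6 × √28 = 3.175, and Φ(3.175 − 2.241) = 82.5%. The t-test gives 81.5%.

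| Setting | Evaluable per arm | Power, t-test | Power, normal approx. |
|---|---|---|---|
| Two-sided 0.05 (= one-sided 0.025), 20% attrition | 44.8 | 80.2% | 81.0% |
| **Two-sided 0.025, 20% attrition (as planned)** | 44.8 | **71.1%** | **72.5%** |
| Two-sided 0.025, 20% attrition, rounded up | 45 | 71.4% | 72.7% |
| Two-sided 0.025, no attrition | 56 | 81.5% | 82.5% |

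**Step 4: detectable effect.** With 45 per arm, two-sided 0.025 and 80% power, the t-test detects d = 0.66.

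**Step 5: three-group F test at 0.025, about 134 evaluable in total.** If both active arms differ from control by 0.6 (f = 0.283), power is 75%. If the three means are evenly spaced over 0.6 (f = 0.245), power is 60%. Neither reaches 80%.

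**The case against.** The strongest reply is that the sample size paragraph never states sidedness. Read alone as a one-sided 2.5% level, it gives 80.2%, and the failure appears only when the data analysis section is read with it. That is true, but it does not help. One-sided 0.025 has the same critical value as an unadjusted two-sided 0.05, so the announced adjustment would have had no effect, and the reading contradicts the two-tailed rule.

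A second reply is that the cause is not proven. This stands. The authors may have used two-sided 0.05, entered 2.5% as one-tailed, or applied the adjustment and forgotten attrition. The first two fit the 56 best. The shortfall is the same whichever it was.

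Third, an F test with f = 0.30 at 0.025 gives about 81% with 134 evaluable. But f = d/2 is the two-group conversion. In three equal arms with a largest pairwise difference of 0.6, f cannot exceed 0.283.

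Fourth, 71% describes a t-test at one time point, whereas the plan is crude and adjusted GEE on repeated measures with multiple imputation. This limits the claim. If 0.6 is on the raw standard deviation and the analysis adjusts for baseline, the effective difference is 0.6/√(1 − r²), where r is the correlation with baseline. Power is then 73% at r = 0.2, 79% at r = 0.4 and 84% at r = 0.5, and it reaches 80% at about r = 0.42. The protocol states no such correlation and does not rest its 80% on one. Imputation does not in itself restore the information lost with missing outcomes.

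Finally, the consequence is moderate: no patient, threshold or analysis changes. That bears on the cost of the fix, not on whether the statement is correct.

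**Conclusion.** The concern holds. On the protocol's own inputs, power is about 71% (72.5% by the normal approximation), not 80%, and the type II error for each comparison with usual care is about 29%, not 20%. The effect detectable with 80% power is 0.66 rather than 0.60.

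This rests on reading 0.6 as a standardised mean difference, a two-sample comparison at one time point, and 20% attrition taken from the 168 recruited. A baseline-adjusted analysis could recover the loss, but only under a correlation that the protocol does not declare. That the Bonferroni adjustment was left out of the calculation is the likely explanation, not an established one.

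**What to change.** Keep 168 and replace the power sentence with one that agrees with the data analysis section, for example:

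> 168 participants randomised (56 per arm, about 45 evaluable per arm after 20% attrition) give 71% power for a standardised difference of 0.6, or 80% power for 0.66, in a two-sample comparison of each intervention with usual care at two-sided 0.025.

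State sidedness and the test in the sample size section itself. If the authors prefer to base power on a baseline-adjusted analysis, they should say so, declare and justify the assumed baseline correlation, and give the power at that value and at lower ones.

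The cost is a change of wording and a less favourable figure. No added patients are needed. Holding to 80% power for 0.6 on the unadjusted basis would instead require 207 randomised, 39 more than planned (207 − 168).
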